### Interventions

The control intervention encompasses web-based activities aimed at promoting healthy lifestyles for active aging (WEB-Health). This intervention includes education on healthy lifestyles to promote active aging (topics: physical activity in old age, effective communication, stress management, technologies, and health). It consists of 3 seminars, delivered in the form of webinars, on a biweekly basis over 6 consecutive weeks, lasting 50-60 minutes each. Each webinar will be led by a qualified mental health professional and delivered live in plenary session through the Zoom platform (Zoom Video Communications, Inc).

The experimental intervention (VSail) includes 12 sessions (2 times a week, for 6 consecutive weeks) with scenarios (virtual environments) dedicated to the sport of sailing. The duration of each session is 50-60 minutes. It is based on the immersive VR software “CEREBRUM” developed by the Cerebrum VR Society. The software represents one of the most recent tools in psychiatric rehabilitation, specifically designed for cognitive remediation. Developed by mental health professionals, “CEREBRUM” is compatible with the “Oculus Quest” VR headset, which carries the CE marking, ensuring adherence to European safety, health, and environmental protection standards. Within the immersive virtual environment, participants interacted with scenarios replicating daily activities in both home and urban settings.

For the present project, the “CEREBRUM” software was further developed through the addition of 4 virtual scenarios specifically designed around the sport of sailing. The decision to add these scenarios was driven by the aim of making the virtual experience during cognitive training more interactive and of simultaneously engaging motor functions. The “CEREBRUM” sailing-based scenarios enable users to move within the virtual space to grasp and manipulate objects (eg, the helm) and to perform specific movements required for executing sailing manoeuvres (eg, approaching the sheet, bending down to reach it, and alternating rapid arm movements to haul the line and adjust the sail). The “CEREBRUM” software comprises exercises of varying difficulty designed to train various cognitive functions, including attention, memory, learning, cognitive estimation, working memory, executive functions, motor abilities, and language. The different degrees of difficulty are designed to adapt to the user’s functional diagnosis. The operator who conducts the intervention must adapt the difficulty level to the user’s residual abilities so that the exercises are neither too easy nor too complex. Each session, after an initial part of welcome, psychoeducation and orientation to the instrument, involves alternating VR exercises for a maximum of 15-20 minutes, positive and corrective feedback, and suggestions of practical homework related to the cognitive function trained during the session that the individual should try during daily life (generalization phase).

### Outcomes

The primary outcomes regard feasibility and include (1) dropout rates, (2) the proportion of recruited participants among those considered eligible, (3) the incidence of potential adverse effects associated with the use of immersive VR technology (eg, nausea, dizziness, visual fatigue, and headache), and (4) the level of perceived satisfaction reported by participants following the experimental intervention.

The secondary outcomes regard cognitive functioning and include (1) executive functions, (2) memory, (3) visuospatial abilities, (4) selective attention, and (5) general cognitive functioning.

The tertiary outcomes regard psychosocial and physical functioning and include (1) QoL, (2) depressive symptoms, (3) anxiety symptoms, (4) regulation of social and biological rhythms, (5) body awareness, (6) levels of physical activity, and (7) mobility.

Also, the following sociodemographic and clinical variables will be collected for each participant: gender and age, marital status, educational attainment, past and current occupational status, history of and current organic physical illnesses, history of and current mental health diagnoses, and current medication use.

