**Primary outcomes (feasibility): the tools and evaluation procedures**
Tolerability, including dropout rates and acceptability, which considers the proportion of recruited participants among those considered eligible. These will be calculated following this timeline: T0 (0 weeks - baseline), T1 (6 weeks), T2 (12 weeks from T1), T3 (24 weeks from T1), T4 (36 weeks from T1), and T5 (48 weeks from T1).Side and secondary effects through the Simulator Sickness Questionnaire (SSQ) [30], a self-report questionnaire including 16 items that evaluate the frequency of unwanted effects due to VR technologies, such as nausea, dizziness, headaches, eye strain, etc. This questionnaire will be administered following this timeline: T0 (0 weeks - baseline) and T1 (6 weeks).The level of satisfaction with the program as a whole, the effect on psychosocial and physical health, assisting and listening abilities demonstrated by the operators, organizational support for activities, and satisfaction with initial expectations by an ad hoc self-report satisfaction questionnaire. This questionnaire will be administered at T1 (6 weeks after T0).

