### Data Analysis, Statistical Power, and Sample Size

The statistical analysis will use SPSS software (version 21; IBM Corp). Descriptive statistics will be calculated for all variables, with nominal variables reported as frequencies and percentages (n; %) and continuous variables as means and SDs (mean, SD).

Given the feasibility-oriented nature of this trial, all analyses of secondary and tertiary outcomes are exploratory and are not intended to provide definitive evidence of effectiveness. The inclusion of multiple cognitive, psychosocial, and physical outcomes is justified by the need to obtain preliminary effect size estimates and variability parameters that will guide the selection and prioritization of outcomes in a future fully powered RCT. Therefore, the analyses of secondary and tertiary outcomes will be interpreted as hypothesis-generating. No formal power calculations for effectiveness end points have been performed, as the current sample size is intended to assess procedural feasibility and parameter estimation rather than hypothesis testing.

To assess baseline homogeneity between the control group and the intervention group, chi-square tests will be used for nominal variables and 1-way ANOVA for continuous variables. Expected differences related to “group,” “time,” and the “group × time” interaction for all dependent variables will be analyzed using a series of multivariate ANOVA. Specifically, repeated-measures ANOVA and multivariate ANOVA will be applied to continuous variables, while the De Castellan test will be used for nominal variables. Bonferroni correction will be applied where appropriate. The assumption of normality for dependent variables will be examined in relation to sphericity, with the Mauchly test used to assess the equality of variances across related group combinations. Cases with missing data will be treated as incomplete and excluded from the analyses. Secondary analyses may be conducted on specific subgroups (eg, by age) and on selected outcomes (eg, individual items from the administered questionnaires).

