Regarding statistical power, it is important to note that no previous RCTs have examined the effects of an immersive VR intervention using virtual sailing scenarios in this population. For this reason, this study is designed as a feasibility and exploratory trial. Although this, the planned sample size is consistent with previous feasibility studies using VR-based paradigms, which have typically enrolled small to moderate cohorts [18,46-48]. On this basis, a total sample of 40 participants (20 per arm) was considered appropriate to assess procedural feasibility, obtain reliable estimates of variability, and capture preliminary effect size signals to inform the design for a fully powered RCT.

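### Satisfaction, a primary feasibility outcome, rests on those who return a form at T1, with no stated provision for participants who withdraw earlier, and so risks overstating satisfaction

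*Protocol article*

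**What the plan says.** The Outcomes section lists four primary feasibility outcomes: dropout, recruitment among those eligible, adverse effects of the VR technology, and "the level of perceived satisfaction reported by participants following the experimental intervention".

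The textbox of tools under Evaluation Tools and Timeline describes the instrument for the last of these as covering the programme overall, its perceived effect on health, the operators, the organisation, and "satisfaction with initial expectations by an ad hoc self-report satisfaction questionnaire". It gives one time point: "This questionnaire will be administered at T1 (6 weeks after T0)". The same textbox has dropout calculated at every assessment from T0 to T5, under "Tolerability, including dropout rates and acceptability, which considers the proportion of recruited participants among those considered eligible".

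The section Data Analysis, Statistical Power, and Sample Size then states: "Cases with missing data will be treated as incomplete and excluded from the analyses". It makes no exception for the feasibility outcomes. On size, the plan says that "a total sample of 40 participants (20 per arm) was considered appropriate to assess procedural feasibility". No expected dropout rate, satisfaction level or threshold appears anywhere in the article.

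**The concern.** Two stated rules combine here. There is a single administration, and cases without complete data are excluded. A participant who withdraws before T1 and returns no form therefore contributes nothing to a primary outcome.

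This missingness may well be informative. The questionnaire asks about the programme itself, and discontent with the programme is one plausible reason for leaving 12 sessions in 6 weeks. The Risk and Benefits section lists nausea, dizziness, headache and visual fatigue as possible effects, and the limitations name varying familiarity with technology. If such reasons drive withdrawal, the satisfaction figure can stay high, or even rise, as retention worsens.

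The section Next Steps for Scale-Up and Implementation makes the full trial depend on the feasibility indicators and plans to revise the dosage and session structure. The views of those who left bear directly on both.

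**Working it through.** **Is there a figure to reproduce?** No. The article states no satisfaction level, dropout rate or threshold, and the sample size is justified by precedent. What follows is an illustration under stated assumptions.

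**Inputs**
- VSail arm: 20 participants (Data Analysis, Statistical Power, and Sample Size). I assume that all 20 start VSail.
- d, the share of the arm without a T1 form: assumed 10%, 20% or 30%, that is 2, 4 or 6 of 20.
- S_R, the proportion satisfied among responders: assumed 90%.
- S_L, the proportion satisfied among leavers without a form: assumed 0% to 50%.
- A satisfied/not-satisfied split: assumed. The article speaks of a level and defines no cut-off.

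**Formula**

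Level over all starters = (1 − d) × S_R + d × S_L

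Overstatement = S_R − level over all starters = d × (S_R − S_L)

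**Results with S_R = 90%**

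| No form | d | Overstatement, S_L = 50% | Overstatement, S_L = 0% | Level over all starters |
|---|---|---|---|---|
| 2 of 20 | 0.10 | 0.10 × 0.40 = 4 points | 0.10 × 0.90 = 9 points | 81-86% |
| 4 of 20 | 0.20 | 0.20 × 0.40 = 8 points | 0.20 × 0.90 = 18 points | 72-82% |
| 6 of 20 | 0.30 | 0.30 × 0.40 = 12 points | 0.30 × 0.90 = 27 points | 63-78% |

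If S_L = S_R the overstatement is d × 0 = 0. If everyone returns a form, d = 0 and it is again 0. With S_R = 80% and the same S_L, the range runs from 0.10 × 0.30 = 3 points to 0.30 × 0.80 = 24 points.

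**In whole participants.** Suppose 4 of 20 return no form and 14 of the 16 responders are satisfied. The responder figure is 14/16 = 88%. Counting the four as not satisfied gives 14/20 = 70%; counting them as satisfied gives 18/20 = 90%. Each missing person is 1/20 = 5 points of the arm.

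**If satisfaction is scored as continuous.** The same formula applies to the mean: overstatement = d × (difference in means). For an assumed difference of 0.5 to 1.5 SD and d of 0.10 to 0.30, it runs from 0.10 × 0.5 = 0.05 SD to 0.30 × 1.5 = 0.45 SD.

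**The case against.** Several points can be made against this, and some of them stand.

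**T1 is a calendar visit.** A reader might infer that satisfaction is collected only from those who complete the programme. The article does not say so. T1 is fixed at 6 weeks after baseline, not by completing 12 sessions, and nothing bars someone who has stopped sessions from attending. Only a participant who leaves the study before T1 is bound to be missed under the stated schedule. This stands.

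**The direction is not established.** A reader might also infer that the figure will be inflated. That needs leavers to be less satisfied. Older people with MCI may leave because of illness or travel, and the Results section mentions difficulty in reaching the facilities regularly. This stands too: the documents support a risk, not a demonstrated bias.

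**The exclusion sentence may not have been written for this outcome.** It follows the repeated-measures text, and satisfaction has a single time point. That is a fair reading, but it changes little. The sentence carries no exception, and a plain summary of the forms received would be conditional on response in any case.

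**Dropout is itself a primary outcome.** Attrition will be visible beside satisfaction, which softens the problem. It shows how many left, not what they thought.

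**A condensed article may leave exit procedures to the full protocol.** That is true of form handling, and the absence of an exit procedure alone would be no finding. The point rests on what is stated: one time point and exclusion of incomplete cases.

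**Operators.** Because the form rates the operators, a reader might infer that answers go back to the person being rated. The section Participants, Recruitment, and Setting assigns assessment and delivery to mental health professionals as a group. It does not say that the same individual does both for a given participant or collects the form, so this is not part of the point.

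**Conclusion.** The point holds as a risk. As planned, the satisfaction result describes those who return a T1 form, and the stated rules would remove everyone else from a primary feasibility outcome. If leavers are less satisfied, the figure is too high by d × (S_R − S_L). Under the assumed 10-30% without a form, 90% satisfied among responders and 0-50% among leavers, that is about 4 to 27 percentage points. The upper end needs both 30% loss and no satisfied leaver. The overstatement is zero if leavers are equally satisfied or are surveyed. None of these rates comes from the article, which supports neither a particular size nor a certain direction.

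This is an inexpensive improvement to how a primary outcome is collected and reported. It does not invalidate the trial.

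**What to change.** 1. State that the missing-data exclusion does not apply to satisfaction.
2. Report the number of responders out of all randomised participants who started VSail, with non-responders shown. If the outcome is dichotomised, define the cut-off and add a bound that counts non-responders as not satisfied. If it is scored as continuous, give the mean among responders with the response rate beside it.
3. Ask participants who stopped sessions for the same form at T1. Ask those who withdraw for it at withdrawal, by telephone or post if they agree. The trial already uses the telephone for recruitment.

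**Cost.** Items 1 and 2 need a few sentences and no new data. Item 3 needs a few extra copies of an existing short form, but timing limits it. At manuscript submission 39 of the planned 40 were enrolled, recruitment was due to end in November 2025, and the pre-post analyses were set for January 2026. It can be applied only to participants for whom it is still possible; for the rest, the reporting change is what remains. The published satisfaction figure may look less favourable.

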### Evaluation Tools and Timeline

Outcomes will be assessed using validated questionnaires, tests, and performance-based measures at predefined time points (Textbox 1).

The tools and evaluation procedures.
**Primary outcomes (feasibility): the tools and evaluation procedures**
Tolerability, including dropout rates and acceptability, which considers the proportion of recruited participants among those considered eligible. These will be calculated following this timeline: T0 (0 weeks - baseline), T1 (6 weeks), T2 (12 weeks from T1), T3 (24 weeks from T1), T4 (36 weeks from T1), and T5 (48 weeks from T1).Side and secondary effects through the Simulator Sickness Questionnaire (SSQ) [30], a self-report questionnaire including 16 items that evaluate the frequency of unwanted effects due to VR technologies, such as nausea, dizziness, headaches, eye strain, etc. This questionnaire will be administered following this timeline: T0 (0 weeks - baseline) and T1 (6 weeks).The level of satisfaction with the program as a whole, the effect on psychosocial and physical health, assisting and listening abilities demonstrated by the operators, organizational support for activities, and satisfaction with initial expectations by an ad hoc self-report satisfaction questionnaire. This questionnaire will be administered at T1 (6 weeks after T0).

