### Randomization and Allocation Concealment

Participants who meet the eligibility criteria will be randomly assigned to one of the two groups: an intervention group and a control group. Randomization will be conducted after baseline assessment. Randomization will be computer-based and concealed. The individuals conducting the randomization procedure will be blinded to participants’ identities and statuses and will not receive any information about them. Participants will be randomly assigned to experimental or control groups in a 1:1 ratio using block randomization. Allocation codes were concealed.

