### Risk and Benefits

The use of immersive VR may be associated with mild and transient side effects, including dizziness, nausea, headaches, visual fatigue, impaired limb coordination, diminished postural stability, a decreased sense of presence, and potentially inappropriate reactions to real-world environments. Nonetheless, significant adverse effects are not expected, as VR is considered a safe and well-tolerated approach, with an extremely low risk of side effects [18,19,22,49-51].

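### The only instrument named for the incidence of VR side effects, a primary outcome, is not timed to VR exposure and is missing for anyone who leaves before T1, so an SSQ-based incidence can be too low

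*Protocol article*

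**What the plan says.** All references are to the protocol article.

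- **Outcome.** The Outcomes section lists as primary outcome (3) "the incidence of potential adverse effects associated with the use of immersive VR technology (eg, nausea, dizziness, visual fatigue, and headache").
- **Instrument.** Textbox 1, under primary outcomes, measures "Side and secondary effects through the Simulator Sickness Questionnaire (SSQ"). It describes this as a 16-item self-report form used to "evaluate the frequency of unwanted effects due to VR technologies, such as nausea, dizziness, headaches, eye strain, etc", and gives no recall window.
- **Timing.** "This questionnaire will be administered following this timeline: T0 (0 weeks - baseline) and T1 (6 weeks"). No other SSQ administration is given.
- **T0 and exposure.** Under Randomization and Allocation Concealment: "Randomization will be conducted after baseline assessment". T0 therefore comes before any VR session in the trial.
- **Exposure.** Interventions describes 12 VSail sessions over 6 weeks, each with at most 15-20 minutes of VR exercises.
- **Expected effects.** Risk and Benefits: "The use of immersive VR may be associated with mild and transient side effects".
- **Satisfaction**, primary outcome (4): "This questionnaire will be administered at T1 (6 weeks after T0").
- **Adverse events.** Adverse Event Reporting says every event will be documented, including its type, onset and resolution dates, severity and possible relationship to the study. It does not say how or when events are elicited, or that they enter primary outcome (3).
- **Missing data.** The data analysis section excludes cases with missing data from the analyses.

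**The concern.** An incidence is the share of exposed people who have the event at any time while exposed. The protocol spreads exposure over 12 short sessions and expects the effects to pass quickly. Yet the form assigned to the outcome is given once before exposure and once at a 6-week visit that need not fall near a session. Symptoms that came and went after an early session may leave no trace in that rating.

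The people without a T1 form are also not a random subset. Someone who leaves the study because VR made them unwell has no post-exposure SSQ and no satisfaction form. If the complete-case rule is applied to these outcomes, that person leaves the denominator as well.

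Both mechanisms push the SSQ-based figure in the favourable direction. The Discussion anticipates good tolerability. It intends the results to shape dosage and session structure in a full trial and, if the intervention proves feasible, to reach policymakers. A side-effect figure that is too low in older adults with MCI would weaken each of those uses.

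**Working it through.** The protocol states no expected incidence, so there is no figure to reproduce. The first step compares schedule with outcome; the other two are illustrations of scale.

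**Step 1. Schedule against outcome.**

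| Item | Stated in the protocol |
|---|---|
| VR sessions between T0 and T1 | 12 |
| SSQ ratings after first exposure | 1 (T1) |
| SSQ ratings tied to a session | none stated |
| SSQ ratings for someone who leaves the study before T1 | none after exposure |
| Other route for side effects | adverse-event records, not linked to this outcome |

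**Step 2. Share ever affected over 12 sessions.** Let p be the risk of symptoms in one session. The protocol gives no such risk, so the values of p are assumptions.

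- Independent sessions: share ever affected = 1 - (1 - p)^12.
- Full dependence within person (the same people are affected every time): share ever affected = p.

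| Assumed p | Full dependence | Independent sessions | Expected number of 20 |
|---|---|---|---|
| 2% | 2% | 1 - 0.98^12 = 21.5% | 0.4 to 4.3 |
| 5% | 5% | 1 - 0.95^12 = 46.0% | 1.0 to 9.2 |
| 10% | 10% | 1 - 0.90^12 = 71.8% | 2.0 to 14.4 |
| 20% | 20% | 1 - 0.80^12 = 93.1% | 4.0 to 18.6 |

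Suppose the T1 rating reflected only symptoms from the last session. It would then show a share p, that is 0.4, 1.0, 2.0 or 4.0 of 20. With independent sessions this is p / [1 - (1 - p)^12] = 9%, 11%, 14% or 22% of those ever affected. With full dependence it is all of them. Two things move the result from there:

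- If participants answer T1 as recall over the 6 weeks, the gap narrows.
- If T1 falls on a day away from any session, transient symptoms can be missed even under full dependence.

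**Step 3. Early leavers.** Take 20 VSail participants and suppose d of them leave the study before T1, all because of sickness. Suppose also that 10% of completers report symptoms at T1. Both are assumptions.

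- Figure from completers only: 10% in every case.
- Share among all exposed: [0.10 × (20 - d) + d] / 20.
  - d = 2: (1.8 + 2)/20 = 19%
  - d = 4: (1.6 + 4)/20 = 28%
  - d = 6: (1.4 + 6)/20 = 37%

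This is an upper-end case, because every leaver is taken to be affected. It needs the complete-case rule to be applied to this outcome.

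**The case against.** The strongest reply is that the trial does record side effects. Every adverse event is to be documented with onset and resolution dates, which suits transient events, and nothing restricts those records to completers. Early leavers also appear in the dropout rate, which is calculated at every time point. A reader might infer that transient sickness, or sickness among leavers, goes uncounted in the trial; the documents do not support that. What stands is narrower: the protocol neither links those records to primary outcome (3) nor separates them from it, and the one instrument it names for that outcome has the timing described.

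Other readings also go too far:

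- **That T1 reflects at most one of the 12 sessions.** The SSQ is said to rate frequency, without a recall window, so T1 could be answered over the whole 6 weeks. Textbox 1 does give recall windows for the depression, anxiety, social rhythm, body awareness and physical activity questionnaires, so the SSQ's window is simply open. Recall of brief symptoms over 6 weeks, in people enrolled for cognitive impairment, is a weak substitute, and it does not help for those who left.
- **That 46% or 72% measures the bias.** Those figures need independent sessions. Susceptibility may well cluster within person, and at the extreme the figures fall to 5% and 10%.
- **That anyone who stops VR misses T1.** T1 is a visit at 6 weeks, and no text says that people who stop sessions are not assessed. The gap concerns those who leave the study.
- **That early leavers are certainly excluded from the incidence.** The missing-data sentence is general, but it sits among the repeated-measures ANOVA methods. Its use for a feasibility count is possible, not stated.
- **That satisfaction is asked at the wrong time.** The outcome is satisfaction after the intervention, so T1 fits. Only non-response is at issue.

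Finally, 39 of the planned 40 participants were enrolled at submission, so adding forms at sessions may come too late for most. This limits the prospective part of the fix, but not the definition of the outcome.

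**Conclusion.** The point holds in limited form. The stated SSQ schedule does not match an incidence of transient effects over 12 exposures, and it leaves no post-exposure SSQ or satisfaction form for anyone who leaves before T1. Both features can make the SSQ-based figure too favourable.

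How much too favourable cannot be determined from the protocol. It depends on the risk per session, on how strongly symptoms cluster within person, on whether T1 is answered as recall, on how close T1 falls to a session, and on how many leave because of sickness. The ranges above rest on assumed values for these and show scale only.

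This is a mismatch between a primary outcome and its named measure. It does not show that the trial fails to record harm. It can be corrected largely in how the outcome is defined and reported, and this should be settled before the pre-post analysis planned for January 2026.

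**What to change.** **For all participants, with no new data:**

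1. Define the incidence as the share of VSail participants with at least one VR session who had either a VR-related event in the adverse-event records or a post-exposure rise in SSQ.
2. Report the number of those participants without a post-exposure SSQ, and keep them in the denominator.
3. Do not present the T1 SSQ alone as the incidence. Label it end-of-programme symptoms.
4. Report satisfaction with the number of non-respondents among those who started VSail.

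**For any sessions still to be delivered:**

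5. Give the SSQ immediately before and after VR at selected sessions, for example the first, middle and last.
6. Give the SSQ and the satisfaction form at withdrawal.

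**Cost.** Items 1 to 4 need only a written definition and a few added counts. Their quality depends on how completely mild events were logged, which the article does not describe and the report should state. Items 5 and 6 add a small respondent burden (a 16-item form already in use, within a 50-60 minute session) and need a minor amendment. With 39 of 40 already enrolled, they may reach few participants.
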